The 1-to-1 education sessions in the CREED AF Intervention arm will be conducted by an exercise practitioner/researcher and will be performed either online, over the phone, or in-person. The sessions will incorporate comprehensive behavioural change and motivational strategies to improve patient adherence and compliance to risk factor modification with the aim of improving both short- and long-term adherence to exercise and lifestyle modification goals and reduce their exposure to lifestyle risk factors (e.g., smoking, alcohol consumption, weight reduction etc.). This will be guided by a participant workbook, and further sign-posting to support groups will be in accordance to individual participant’s requirements. A full compliance of education sessions is at least 2 sessions (of a total of 3; 66.7%) at each prehabilitation and rehabilitation intervention.

- 1. **Follow-up data**

In addition to cardiopulmonary exercise testing at 10 weeks follow-up post-ablation, all patients will also repeat the baseline questionnaires to assess their HRQoL, including the EQ-5D-5L, SF-36 and AFEQT, at significant intervals of the intervention journey (as outlined in the Schedule of Events). To assess for AF recurrence and burden, 7-day Holter ECG monitoring will be placed on patients at the 10 weeks and 12 months post-ablation follow-up appointments. The 10-week (±2 week) period will be seen as equivalent to a 3-month blanking period that is normally considered post-ablation in which presence of AF is not seen as a recurrence. The definition of an AF recurrence post-ablation will be an arrhythmia with the characteristics of AF that is either captured on a 12-lead ECG or documented to last for at least 30 seconds on ECG monitoring (1). At 12 months post-ablation, a retrospective review of medical records will be completed to collect data for study defined MACE. This will include, but will not be limited to, a review of clinic letters, medical coding, and A&E records.

- 1. **End of Study Definition**

The end of study definition will be when the last participant has completed their 12-month follow-up appointment and data collection post-ablation.

- 1. **Assessment and Management of Risk**

In keeping with UHCW SOPs, a risk assessment will be implemented, focusing on ensuring safe exercise assessment and prescription for people with AF. Primarily this will involve undertaking appropriate pre-exercise screening; an assessment to ensure the participant can take part in the intervention, both at the Atrium Health Centre, and at their home safely whilst also making sure that they can safely take part in the cardiopulmonary exercise tests. Also, that there will be the provision of appropriately trained staff, suitable facilities, remote supervision, and a comprehensive emergency strategy, with thorough clinical procedures for implementation. Participants will be advised initially to have another adult present at home when carrying out exercises as part of the intervention.

CPET will take place in a UKAS accredited IQIPS standard laboratory. A fully trained member of the research team will run these tests. If a participant is identified to be contraindicated to an exercise test, then their eligibility for the study will be reviewed (i.e., whether the contraindication is temporary in preventing an exercise test).

Physical activity carries a very small risk for patients with AF. Physical activity is likely to cause tiredness, breathlessness, and sore muscles however this is to be expected when starting a new exercise programme and should not be treated as adverse events.

The standard ablation procedure will be carried out by qualified staff members at UHCW. Ablation carries a small risk of further complications which are outlined below:

- <1% risk of vascular injury (including needing surgery)
- 1% risk of pericardial effusion/tamponade
- ~1% risk of stroke
- ~1% risk of phrenic nerve injury
- <1% risk of AV block needing pacing
- 0.5% risk of pulmonary vein stenosis
- Risk of needing emergency cardiac surgery (1:400)
- Other small risks: needing blood transfusion

Any of the above events that occur during the CREED AF study following an AF procedure will be monitored by the trial team and recorded as an adverse outcome of ablation. If it becomes apparent that the CREED AF intervention group are experiencing a statistically significant greater number of these events than the control, then this will be raised and reported in line with local Trust SOPs and reported to the REC as appropriate.

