|  | To explore if CREED AF intervention has an impact on the short- and long-term recurrence of AF post-ablation and the need for redo-AF ablation. | AF recurrence and burden from data collected from a 1–7-day(s) cardiac Holter monitoring at 10 weeks (±2 weeks) and 12 months (±4 weeks) post ablation, and requirement for redo-AF ablation as documented in medical records reviewed at 12 months post-ablation. |
|  | To explore the impact of CREED AF intervention on relevant major adverse cardiovascular events (MACE) in AF patients. | MACE at 12 months post-ablation, defined as:   1. Hospital admission related to AF 2. Non-fatal myocardial infarction 3. Non-fatal stroke 4. Cardiovascular death 5. All-cause mortality |

Key Words: **AF ablation, Pulmonary vein isolation, VO2peak**

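### The protocol assesses AF recurrence on the 10-week Holter but also treats the 10-week (±2 week) period as blanking, and does not fix when recurrence starts to count

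*Protocol*

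**What the plan says.** The Study Summary lists as a secondary objective the "impact on the short- and long-term recurrence of AF post-ablation and the need for redo-AF ablation". Its outcome measure is "cardiac Holter monitoring at 10 weeks (±2 weeks) and 12 months (±4 weeks) post ablation", with redo ablation taken from records at 12 months. Section 5 repeats both Holter time points and says the monitor is fitted at the 10-week and 12-month visits.

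Three sentences in section 9.12 (Follow-up data) bear on the point:

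- Purpose of the recordings: "To assess for AF recurrence and burden, 7-day Holter ECG monitoring will be placed on patients at the 10 weeks and 12 months" after ablation.
- Blanking: "The 10-week (±2 week) period will be seen as equivalent to a 3-month blanking period", described as the "blanking period that is normally considered post-ablation in which presence of AF is not seen as a recurrence".
- The event: an arrhythmia with the features of AF, "captured on a 12-lead ECG or documented to last for at least 30 seconds on ECG monitoring". No date is given from which such an event counts.

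Section 10.5 plans Kaplan-Meier proportions of AF events by arm and a time-to-event estimate from the Holter. It does not mention blanking.

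**The concern.** The blanking sentence names its period in the same terms, 10 weeks plus or minus 2, that the protocol uses for the visit at which the first Holter is fitted. That Holter is the only scheduled short-term measure of recurrence. So one section makes a recording a recurrence assessment and then appears to say that AF in the same period is not recurrence.

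What is at stake is whether an AF episode seen around weeks 8 to 13 enters the recurrence proportion and the time-to-event curve. If blanking ends at a date that depends on the appointment, the same episode on the same day after ablation can count in one participant and be ignored in another. If appointment timing differs by arm, so does the rule.

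**Working it through.** The plan states no figure to reproduce here. The check is a calendar comparison, followed by a comparison of visit timing by arm.

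**Inputs.** The visit window is 10 ± 2 weeks (Study Summary, sections 5 and 9.12). The Holter lasts 7 days (section 9.12; the Study Summary and section 5 allow 1 to 7). Exercise restarts only after a 2-week recovery and runs for 6 to 8 weeks (section 4, Intervention). In the intervention arm the 10-week assessment falls two weeks behind the final exercise session (section 5, primary outcome).

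**Step 1: the window in days.** (10 − 2) × 7 = 56 and (10 + 2) × 7 = 84, a spread of 28 days.

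**Step 2: how much of a 7-day recording counts.** For a monitor fitted on day s and blanking ending on day B, counted days = max(0, s + 7 − max(s, B)). Three months is taken as 365.25 / 4 = 91.3 days (assumed).

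| End of blanking | Fitted week 8 (days 56–63) | Fitted week 10 (days 70–77) | Fitted week 12 (days 84–91) |
|---|---|---|---|
| 3 months (day 91.3) | 0 | 0 | 0 |
| End of visit window (day 84) | 0 | 0 | 7 |
| Fixed 10 weeks (day 70) | 0 | 7 | 7 |
| Participant's own visit | 7 | 7 | 7 |

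A 1-day recording gives the same pattern, with 1 in place of 7. The second row is closest to the literal reading: AF found inside the 10 ± 2 week period is blanked, and only recording days that run past day 84 escape.

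**Step 3: timing by arm if blanking ends at the participant's own visit.**

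- Intervention: last session at week 2 + 6 = 8 to week 2 + 8 = 10; visit two weeks later, at weeks 10 to 12 (days 70 to 84).
- Control: no link to exercise; any time in weeks 8 to 12 (days 56 to 84).

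Between day 56 and day 70 (14 days), AF can therefore count as recurrence in a control participant seen early. It is blanked in an intervention participant who keeps to the schedule. For example, AF in week 9 counts for a control participant seen at week 8 and does not count for an intervention participant seen at week 10. Any such imbalance would favour the intervention.

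**The case against.** The strongest reply is that the sentence has a coherent reading. The interval from ablation to the 10-week visit stands in for the customary 3 months. The monitor is fitted at that visit and records forward, so blanking is over when recording begins and AF of at least 30 seconds counts. Short-term recurrence can then have events, and nothing is contradicted. This stands: the literal conflict is one reading, not the only one. It does not rescue the rule, because blanking then ends on a different day for each participant, with the possible difference by arm shown in step 3.

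It can also be said that both arms share the same ±2-week window, that 4 weeks is small against 12 months, and that the size of any difference by arm is unknown. The last point is right, since the protocol cannot show actual visit dates. But the window is common to both arms only on paper, because section 5 ties the intervention visit to the end of training.

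Time origin and the handling of single recordings in a Kaplan-Meier analysis are usual content for a statistical analysis plan, so the silence of section 10.5 is not itself a fault. The point rests on a rule that section 9.12 does state and that fits badly with its own endpoint.

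A reader might go further and infer that recurrence is undefined, that the short-term endpoint can have no events, or that all AF on the 10-week Holter would be misclassified. The protocol does not support this. The event is defined; only the date from which it counts is open. The other two inferences hold only if blanking runs through the whole recording, for instance to a full 3 months. Section 9.12 cites 3 months as customary and puts its own 10-week period in its place, so showing that weeks 8 to 12 precede 3 months does not settle the matter.

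**Conclusion.** The point holds as an unresolved rule with two readings, both unsatisfactory. On the literal reading, section 9.12 conflicts with the short-term recurrence objective. On the alternative, the end of blanking floats over 28 days and can differ by arm.

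The size is all or nothing for the recording: 0 or 7 of its 7 days in each case worked above. The number of AF episodes affected cannot be estimated from the protocol. The arm comparison assumes that intervention participants complete at least 6 weeks of post-ablation sessions and are seen two weeks later; early stopping or irregular booking would weaken it.

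The definition of the recurrence event, AF burden at 10 weeks and the 12-month Holter assessment are untouched, as are the VO2peak analysis and the sample size. Because this is a secondary objective framed as exploratory, the severity is moderate.

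**What to change.** Reconcile the Study Summary, section 5, section 9.12 and section 10.5 as follows:

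1. Set one end of blanking at a fixed number of days after ablation, the same for every participant and both arms.
2. Start at-risk time for the recurrence analysis on that day.
3. State whether AF on the 10-week Holter counts as recurrence or is reported, by arm, only as early AF and burden.
4. Word the short-term recurrence objective to match.

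Settle this before any 10-week data are seen by arm. Section 10.4 has the primary endpoint analysis presented before 12-month follow-up is complete, and a reading chosen after that could be said to follow the results.

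The cost is wording in the protocol and the analysis plan, with the same recordings and no new procedure. The downside is that, if blanking is set to cover the 10-week Holter, fewer events will be labelled recurrence.

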# **STATISTICS AND DATA ANALYSIS**

- 1. **Sample Size Calculation**

The sample size calculation was based on the analysis of the change in the primary outcome (VO_2peak_) at 10 weeks post-AF ablation from baseline. Previous studies investigated VO_2peak_ at 6 months post-ablation, which we assume to be similar at 10 weeks post-ablation. Based on Kato *et al.*, we can assume that the VO_2peak_ standard deviation is around 3ml/kg/min at baseline and 4ml/kg/min at 10 weeks post-ablation (63). As the correlation between the time points is unknown, we assume a value of r=0.5. Consequently, the standard deviation of the difference from 10 weeks post-ablation to baseline is around 3.6ml/kg/min. Based on Fiala *et al.* we can assume that the change in VO_2peak_ will be around 2ml/kg/min due to AF ablation and a further 4ml/kg/min (63,64) due to cardiac rehabilitation (which comprises pre- and post-AF ablation rehabilitation). Therefore, the difference between the intervention arm and standard care is expected to be 4ml/kg/min at 10 weeks (±2 weeks) post AF ablation compared with baseline. To detect a conservative difference of 2.5ml/kg/min (an increase in 2.5ml/kg/min VO_2peak_ in the intervention arm from standard care, at 10 weeks post-ablation compared with baseline) at 5% significance level, with 90% power, we require 88 patients in total. To allow a drop-out rate of 20%, we will recruit 106 patients, with 53 randomly allocated to each group.

- 1. **Planned Recruitment Rate**

Participants who are referred for first-time AF ablation at UHCW NHS Trust with AF symptoms and meet the remaining inclusion/exclusion criteria will be eligible for the study. At UHCW we are seeing ~300 patients each year at UHCW for first-time AF ablation and it is predicted that ~200 of these patients will be eligible. We will be aiming to recruit around 1-3 patients per week over an ∼16-month period to recruit the participant population within the ∼16-month recruitment period.

- 1. **Statistical Considerations**

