# **ADVERSE EVENT MANAGEMENT**

- 1. **Adverse Events**

An Adverse Event (AE) is defined as any untoward medical occurrence involving a participant, which does not necessarily have a causal relationship with the intervention or trial.

**Expected** **AEs,** related to the exercise outcome assessments or the exercise intervention, include ‘normal’ levels (for the individual) of:

- Breathlessness
- light headedness/dizziness
- muscle and joint stiffness/soreness
- tiredness/fatigue

There are a few AEs which are expected following AF ablation and occur after roughly 2-4% of all AF ablation cases. These AEs are listed below:

- Vascular injury
- Pericardial effusion/tamponade
- Stroke/Transient Ischaemic Attack
- Myocardial Infarction
- Phrenic nerve injury
- Atrioventricular block
- Pulmonary vein stenosis

Of these conditions there is a small risk (1:400) of requiring further cardiac surgery or a blood transfusion. Each AE will be assessed by the CI or a delegated clinician to assess causality to the CREED AF intervention. In the unlikely event that it is decided that one of the above post AF ablation conditions is related to the CREED AF intervention this will be reported as such in line with local Trust policy and national safety reporting guidelines.

Recording procedures will be the same for both trial groups. Expected AEs will be recorded on the CRF (AE form).

**Unexpected AEs** related to the exercise outcome assessments or the exercise intervention for both the intervention and usual care groups, will be recorded on the appropriate CRF (AE form) and returned routinely to UHCW. Unexpected AEs will be logged and reported at TMG meetings. Should multiple of the same unexpected AE occur during the trial period then this will trigger the TMG to review the study procedures to see if there are any changes that need to be implemented.

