| Unlikely to be related | There is little evidence to suggest there is a causal relationship (e.g. the event did not occur within a reasonable time after administration of the trial intervention). There is another reasonable explanation for the event (e.g. the patient’s clinical condition, other concomitant treatment). |
| Possible relationship | There is some evidence to suggest a causal relationship (e.g. because the event occurs within a reasonable time after administration of the trial intervention). However, the influence of other factors may have contributed to the event (e.g. the patient’s clinical condition, other concomitant treatments). |
| Probable relationship | There is evidence to suggest a causal relationship and the influence of other factors is unlikely. |
| Definitely related | There is clear evidence to suggest a causal relationship and other possible contributing factors can be ruled out. |

To establish causality, the following information should be collected for each SAE:

- full details in medical terms and case description
- event duration (start and end dates, if applicable)
- action taken
- outcome
- seriousness criteria
- causality (i.e. relatedness to intervention), in the opinion of the PI
- whether the event would be considered expected or unexpected

SAEs that are deemed to be unexpected and possibly, probably or definitely related to the trial interventions or outcomes assessments, will be notified to the Research Ethics Committee (REC) within 15 days. All such events will be reported to the TMG at their next meeting.

Any change of condition or other follow-up information should be communicated to the Sponsor as soon as it is available or at least within 24 hours of the information becoming available. Events will be followed until resolution or a final outcome has been reached. A member of the PI’s trial team will be instructed to closely monitor each participant who experiences a SAE, until the outcome of the SAE has been determined.

- 1. **Responsibilities**

*Chief Investigator/delegate or independent clinical reviewer:*

- Clinical oversight of the safety of patients participating in the trial, including an ongoing review of the risk / benefit.
- Using clinical judgement in assigning seriousness and causality of SAEs where it has not been possible to obtain local medical assessment.
- Using clinical judgement in assigning expectedness.
- Immediate review of all related and unexpected SAEs.

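### The protocol's only between-arm trigger for ablation complications waits for statistical significance, which a moderate excess will rarely reach with 53 patients per arm

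*Protocol*

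**What the plan says.** Section 9.14 (Assessment and Management of Risk) lists the complications of ablation with their risks, for example "1% risk of pericardial effusion/tamponade" and about "1% risk of stroke". The other listed risks are about 1% or less. The trial team will monitor these events and record them as adverse outcomes of ablation. The comparative rule comes next: "If it becomes apparent that the CREED AF intervention group are experiencing a statistically significant greater number of these events than the control". The stated consequence is that the matter is raised under local Trust SOPs and, where appropriate, goes to the REC. No test, level, sidedness or number of looks is given, and the text does not say whether events are compared singly or pooled.

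Section 13.1 (Adverse Events) lists largely the same complications as expected after ablation and says that they "occur after roughly 2-4% of all AF ablation cases". Each adverse event is assessed for causality to the programme. A listed complication judged related is reported under Trust policy and national guidelines, an outcome that the section calls unlikely.

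Section 13.2 (Serious Adverse Events) sends to the REC within 15 days "SAEs that are deemed to be unexpected and possibly, probably or definitely related to the trial interventions or outcomes assessments". Section 13.3 (Responsibilities) has the TMG review safety data periodically and gives the chief investigator, a delegate or an independent clinical reviewer an ongoing review of risk and benefit.

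On size, Section 10.1 states "we will recruit 106 patients, with 53 randomly allocated to each group".

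**The concern.** If exercise around the time of ablation did harm, it would most plausibly show as a higher frequency of complications that also occur without exercise. A single tamponade or vascular injury looks the same in either arm, so individual causality review is poorly placed to show that a known complication has become more common. A comparison of the arms is the natural tool.

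The one rule that makes this comparison is tied to a significance test in a trial sized for VO2peak. If the test has almost no power at these event rates, the rule gives little protection, and a non-significant result may be taken as reassurance.

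**Working it through.** **Inputs from the protocol.** 53 per arm, allocated 1:1 (Sections 10.1 and 9.6). Single complications at about 1% or less (Section 9.14). All complications together at roughly 2-4% (Section 13.1).

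**Assumptions.** A 5% level (the protocol states 5% only for VO2peak), one analysis at the end, and complete data. Risk ratios of two, three and five are illustrative, because the protocol gives no expected harm ratio.

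**The plan's own figure.** The SD of change is √(3² + 4² − 2 × 0.5 × 3 × 4) = √13 = 3.61. With a difference of 2.5, two-sided 5% and 90% power, n per arm = 2 × (1.960 + 1.282)² × 3.6² / 2.5² = 43.6, so 44 per arm and 88 in total, as stated. The trial size was therefore set by VO2peak. The protocol gives no power for the safety trigger.

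**Expected control-arm events.** 53 × 0.01 = 0.53 for one complication at 1%. Pooled, 53 × 0.02 = 1.06 to 53 × 0.04 = 2.12.

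**Smallest splits that count as significant (intervention v control, 53 per arm):**

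| Control events | Two-sided Fisher | One-sided Fisher |
|---|---|---|
| 0 | 6 (p = 0.027); 5 gives 0.057 | 5 (p = 0.028) |
| 1 | 8 (p = 0.031); 7 gives 0.060 | 7 (p = 0.030) |
| 2 | 10 (p = 0.028); 9 gives 0.052 | 8 (p = 0.046) |

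**Chance that the trigger fires.** P = Σ Bin(i; 53, p_I) × Bin(c; 53, p_C), summed over all pairs with i > c and p ≤ 0.05.

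| Control to intervention risk | Two-sided Fisher | One-sided Fisher | One-sided z, uncorrected |
|---|---|---|---|
| 1% to 2% (single event) | 0.04% | 0.25% | 5.4% |
| 1% to 3% (single event) | 0.3% | 1.3% | 13.1% |
| 2% to 4% (pooled) | 0.7% | 2.3% | 14.6% |
| 4% to 8% (pooled) | 4.6% | 9.9% | 24.0% |
| 2% to 6% (pooled) | 3.8% | 8.9% | 30.0% |
| 4% to 12% (pooled) | 18.5% | 31.2% | 47.9% |
| 4% to 20% (pooled) | 63% | 77% | 85% |

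The last column is the most lenient test tried. Even there, a pooled doubling from 4% is missed in 76% of trials.

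**Sensitivity.** With 42 per arm (53 × 0.8 = 42.4), a doubling fires in 0.01% to 2.8% of trials across control risks of 1% to 4% (two-sided Fisher). If the separate risks in Section 9.14 are summed with each figure below 1% taken as 1% and no overlap, the pooled rate is 1 + 1 + 1 + 1 + 1 + 0.5 + 0.25 = 5.75%. At that upper bound a doubling fires in 8.9% (two-sided Fisher) or 17.3% (one-sided), and a tripling in 33% or 49%.

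**Size needed.** For 80% power to detect a doubling at two-sided 5%, the trial would need 2,319, 1,141 or 553 per arm from control risks of 1%, 2% or 4%.

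**The two event lists.** Myocardial infarction and transient ischaemic attack are expected post-ablation events in Section 13.1 but are not in the Section 9.14 list to which the trigger refers.

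**The case against.** A reader might infer that a real harm of the programme would go unreported. The protocol does not support that. Section 9.14 states one condition for raising an excess and does not say that it is the only one, or that non-significance is an all-clear. Section 13.1 has every adverse event assessed for causality, and a listed complication judged related is reported whether or not it was expected. Section 13.2 has the chief investigator review events in the intervention group up to the 10-week assessment. Section 13.3 provides TMG review and ongoing review of risk and benefit. None of these needs a p-value.

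That stands, but these routes only partly fill the gap. The REC route in Section 13.2 requires an unexpected event, and these complications are labelled expected. The repeat-event trigger in Section 13.1 also covers unexpected events only. The periodic TMG review has no stated content or by-arm table.

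A second objection is that the figures depend on the test. The wording is directional, so a one-sided test is a fair reading and roughly doubles or triples the chance for the pooled doublings and triplings. Hence the range above. It leaves a moderate excess unlikely to fire, but it means that the trigger is not blind to very large harm.

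Myocardial infarction and stroke are also collected by arm as components of the MACE outcome, so the list mismatch is a minor matter of consistency.

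**Conclusion.** The concern holds in a limited form. The only explicit between-arm trigger for ablation complications uses an unspecified significance test. With 53 per arm and 2-4% combined risk, it would detect a true doubling in 0.7-4.6% of trials (two-sided Fisher) or 2.3-9.9% (one-sided), and a tripling in 3.8-18.5% or 8.9-31%. Within that range of control risks, firing becomes more likely than not only for an extreme harm: a rise from 4% to 20% fires in 63% by two-sided Fisher.

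A moderate excess would therefore not normally meet the rule and would rest on individual causality judgement or unstructured TMG review. These results assume a 5% level, one final analysis and complete data. This is a weak safety rule that is cheap to repair. It is not evidence that harms would be hidden.

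**What to change.** In Section 9.14, delete the statistical significance condition. State that the listed complications are tabulated by arm at the periodic safety review already provided for in Section 13.3. State also that a numerical excess in the intervention arm is reviewed by the chief investigator or the independent clinical reviewer, and raised with the sponsor and the REC on clinical judgement, without a p-value. Reconcile the event lists in Sections 9.14 and 13.1, where myocardial infarction and transient ischaemic attack appear only in the latter.

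The cost is a wording change and one table. There are two downsides. Some chance imbalances will be reviewed and prove to be noise, although with one or two control-arm events expected the burden is small. The reviewers will also see accumulating counts by arm, and the TMG includes co-investigators, one of whom carries out most of the primary analysis. The table should therefore be confined to safety events and kept from the exercise physiologists who are blinded for the 10-week test.
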